## Abstract

**Background:**

The use of lymph node (LN) tracers can help obtain a complete dissection of the lymph nodes and increase the detection rate of LNs and metastatic LNs. Carbon nanoparticle suspension injection (CNSI) and indocyanine green (ICG) have been widely used in radical gastrectomy in recent years. Nevertheless, the comparison of their clinical effects has not been studied.

**Method/design:**

The FUTURE-01 trial will be the first randomized, open-label, single-center trial to compare CNSI and ICG. The study started in 2021 and enrolled 96 patients according to a prior sample size calculation. The primary outcome is the number of LNs retrieved. The secondary outcomes are LN staining rate, LN metastasis rate, stained LN metastasis rate, perioperative recovery and survival.

**Conclusion:**

By comparing the safety and efficacy of CNSI and ICG tracer-guided LN dissection in patients with gastric cancer, we can determine the most appropriate LN tracer at present. With the help of LN tracers, the operation is simplified, and the prognosis of these patients is improved. Our study is a prospective exploration of the safety, efficacy, and prognosis of CNSI and ICG.

**Clinical trial registration:**

https://clinicaltrials.gov/ct2/show/NCT05229874?cond=NCT05229874&draw=2&rank=1, identifier NCT05229874.

## Introduction

1

Gastric cancer (GC) is one of the most common malignancies worldwide (1). Despite the global downward trends in the GC incidence and mortality rates, GC remains one of the most common causes of death by cancer worldwide and ranks second (2).

For GC, complete resection with standardized LN dissection (D2) is important (3). Although LN dissection is deemed the crucial step in radical gastrectomy, there is no consensus regarding the number of LNs detected worldwide (4–6). The quality of LN dissection should be evaluated by the number of LNs detected, and more detection of LNs can reduce the N staging bias and prolong the GC patient prognosis (7–9).

D2 LN dissection is complex and tricky, and it is performed by removing perivascular fat and the LNs containing adipose baring fat tissue. In the process of lymphadenectomy in gastrectomy, one of the common and severe intraoperative complications is vessel injury. With the aim of easing the difficulty of LN dissection, an increasing number of surgeons are trying to use LN tracers to make the affected LNs distinct. Initially, surgeons used methylene blueand tattoo ink as LN tracers (10). Because of the difficulty of time limitations and low resolution, researchers have gradually abandoned the use of methylene blue.

Currently, two kinds of novel LN tracers have been monitored by endoscopy experts and surgeons. One is carbon nanoparticle suspension injection (CNSI), and the other is indocyanine green (ICG). In 2004, the CNSI (Carnaline, Chongqing Lummy Pharmaceutical Co., Ltd) made in China was launched, which reduced the price of CNSI and the cost medical expenditure and promoted the development of LN tracers. This product is a stable suspension of carbon nanoparticles 150 nm in diameter, which are smaller than the lymphatic capillary endothelial cell gap (120-500 nm) and larger than the capillary endothelial cell gap (30-50 nm) (11). Therefore, following their injection into the submucosa of the gastric wall around the tumor, the carbon nanoparticles rapidly captured by macrophages cannot enter into the blood vessels but enter into the lymphatic vessels and accumulate in the LNs (12). Moreover, CNSI with the features of black and strong colored ability makes the LNs more readily identified and makes the procedure easier. In addition, CNSI is characterized by slow metabolism and can be observed *in vivo* after approximately 3-4 months. Multiple studies have reported that CNSI has a respectably high safety profile, and no significant adverse effects were seen while the detection rate of LNs and metastatic LNs was increased (11, 13). Additionally, researchers have found no suggestion of increased complication rates or operating time.

ICG, as a kind of fluorescent dye, can be applied intraoperatively and used to sort LNs in postoperative specimens. When injected into the submucosa of the gastric wall of GC patients, ICG combines with serum albumin in the circulation and can be found in the LNs. Once excited by infrared light (wavelength, 750–810 nm), ICG can emit infrared fluorescence (peak wavelength, approximately 840 nm), so ICG fluorescence imaging can guide intraoperative LN dissection (14, 15). ICG fluorescence imaging can be performed successfully under a laparoscopic or robotic imaging system (16). Compared with other dyes, ICG fluorescence imaging with better tissue penetration has the potential to identify the LNs shaded by hypertrophic adipose tissue. ICG-guided D2 LN dissection has become a novel hot topic explored by an increasing number of gastrointestinal surgeons. In addition, ICG fluorescence imaging increases the number of LNs retrieved and exhibits a good clinical efficacy and safety profile (15–18).

Concerning the LN metastasis rates, there was not much difference between the CNSI, ICG, and control groups. Hence, we concluded that CNSI was more likely to be the best LN tracer at present. However, this is a retrospective single-center study that includes the well-known limitations of such a study design. It is therefore worthwhile to carry out a prospectively designed study to compare the safety and efficacy of CNSI and ICG tracer-guided LN dissection during radical gastrectomy.

The present study therefore aims to compare the safety and efficacy of CNSI and ICG tracer-guided LN dissection during radical gastrectomy using a randomized clinical trial design and to provide a theoretical basis for further investigation.

## Methods and analysis

2

### Study design

2.1

The current study is a prospective, randomized, open label, single-center, noninferiority clinical trial. The study takes place in the Fourth Hospital of Hebei Medical University. Patient enrollment started on 20 January 2021, and the trial is expected to end on January 20 2025. **Figure 1** summarizes the design of the trial, and each of the trial aspects is described in detail below.

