### Sample size

2.7

The sample size for this study was calculated based on previous research by our team and computed by PASS version 11. Eligible subjects were randomly assigned (1:1) into the CNSI group and the ICG group. All analyses were two-sided with α=0.05 and β=0.80. the prospective mean number of the LNs retrieved in the CNSI group was 56.93. The prospective mean number of the LNs retrieved in the ICG group was 50.52. The total sample size was 96 (48 per group) after taking into account a 10% dropout rate in each group. The planned recruitment period is 1 year, and the follow-up duration is 3 years.

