### Data collection and analysis

2.8

Designated and trained surgeons collect the data from the pathology reports and operative reports. The focus of the data should contain clear information about the tumor location, tumor size, histopathologic type, tumor differentiation degree, Lauren classification, vascular tumor embolus, nerve invasion, immunohistochemistry results and pathological findings of the LNs at each station. Long-term prognosis data are collected *via* follow-up up until 3 years after the surgical operations. The follow-up should consist of a 3-month interval from 0–2 years and a 6-month interval in the third year. The main follow-up items included routine physical examination, tumor marker detection (CEA, CA199, CA724 and AFP), abdominal CT, and annual electronic gastroscopy. The follow-up included an outpatient follow-up, a telephone follow-up and a short message platform follow-up. Further evaluation and treatment should be performed if relapse occurs.

The purpose of this study is to compare the safety and efficacy of CNSI and ICG during radical gastrectomy. The primary objective is to determine the number of LNs retrieved. Comparability analysis will be performed on the baseline data to determine whether the two groups are comparable. The number of patients, mean, standard deviation, median, maximum, and minimum will be listed. Descriptive data will be presented as the mean ± SD, while categorical data will be presented as the number and percentage (%). The independent samples t test or nonparametric test will be used to analyze continuous data, and the chi-square test or Fisher’s exact test will be used to analyze categorical variables. It is valuable to analyze the influence of CNSI (ICG) staining or other factors on the number of LNs detected according to the statistical analysis. We can also research the effect of CNSI (ICG) staining on the operative time, intraoperative bleeding volume, intraoperative transfusion volume and postoperative complications. Survival analysis will be performed using the Kaplan−Meier method, and the log rank test will be used to test the difference in survival rates between the two groups. SPSS 26.0 statistical software will be used for statistical analysis. P<0.05 will be considered to indicate statistically significant differences.

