There are a number of previous reviews on the effectiveness of CNSI and ICG. Chen pointed out that their team analyzed 129 GC patients in the ICG group and 129 control subjects and concluded that ICG tracer-guided LN dissection enabled the retrieval of a higher number of LNs (16). Two retrospective analyses found that fluorescence lymphography has high sensitivity and negative predictive value for the diagnosis of LN metastasis. Fluorescent lymphography-guided lymphadenectomy appears to be a reasonable alternative to conventional systematic lymphadenectomy for gastric cancer (23, 24). Similarly, in accordance with the study of Yan, carbon nanoparticles have the same efficacy and safety as a LN tracer in the clinic (11). Li et al. and our team found that CNSI is a safe material. Surgeons could harvest more LNs in patients with GC. The harvest of an increased number of smaller diameters of LNs may be beneficial. CNSI is associated with facilitating the dissection of all positive LNs, which could improve surgical quality (13, 25). However, very few studies have focused on the comparison of CNSI and ICG. A retrospective study recently conducted by our team suggested that the mean numbers of LNs and micro LNs retrieved in the CNSI group were higher than those in the ICG and control groups, and there were no differences between the ICG and control groups (15).

Whether the results of retrospective analysis can be confirmed by prospective randomized controlled clinical trials still needs to be further studied. Therefore, we are currently conducting a clinical trial to compare CNSI and ICG in detail to choose the optimal and suitable LN tracer for radical gastrectomy.

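### Section 2.1 calls the trial noninferiority, but its sample size and planned test are those of a two-sided difference trial, and that test cannot support a noninferiority conclusion

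*Protocol article*

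**What the plan says.** Four places in the protocol article bear on the type of trial.

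- Section 2.1 (Study design): "The current study is a prospective, randomized, open label, single-center, noninferiority clinical trial". The word noninferiority appears nowhere else in the article.
- Section 2.7 (Sample size): "All analyses were two-sided with α=0.05 and β=0.80". The planning values are "the prospective mean number of the LNs retrieved in the CNSI group was 56.93" and "The prospective mean number of the LNs retrieved in the ICG group was 50.52". The result is "The total sample size was 96 (48 per group) after taking into account a 10% dropout rate in each group".
- Section 2.8 (Data collection and analysis): continuous outcomes are compared by a two-sample t test or a nonparametric alternative, and "P<0.05 will be considered to indicate statistically significant differences".
- Section 3 (Discussion): the trial is being run "to choose the optimal and suitable LN tracer for radical gastrectomy".

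The primary outcome, in section 2.5, is the number of lymph nodes retrieved.

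**The concern.** A noninferiority trial and a difference trial answer different questions. A noninferiority trial asks whether a confidence limit excludes a loss larger than a stated margin. A difference trial asks whether equality can be rejected. Section 2.1 names the first, while sections 2.7 and 2.8 describe the second.

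The two lead to different conclusions when the result is not significant. In the difference trial that result is inconclusive. Under a noninferiority label, a reader may take it as showing that one tracer is no worse than the other, although the test never examined that. The article reports a trial with open treatment, unconcealed allocation (section 2.3) and 96 patients enrolled (Abstract). A margin chosen after outcome data had been seen would carry little weight. What is at stake is how the primary result may be worded.

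**Working it through.** **Inputs from section 2.7.** Expected means 56.93 (CNSI) and 50.52 (ICG), so the difference is 56.93 − 50.52 = 6.41 nodes. Two-sided α = 0.05. The stated β of 0.80 is read as power 0.80. There are 48 per arm with 10% dropout: 48 × 0.9 = 43.2, or about 43 evaluable per arm. No SD is given.

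**The plan's own figure.** Without an SD, 96 cannot be reproduced from the stated inputs. The SD that would produce it can be found by solving n = 2(1.960 + 0.842)² SD² / 6.41² for n = 43:

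- SD = 6.41 / (2.802 × √(2/43)) = 6.41 / (2.802 × 0.2157) ≈ 10.6. With the t distribution it is about 10.5.
- Check at SD 10.5: n = 2 × 7.85 × 110.25 / 41.09 ≈ 42.1, rounded up to 43. Then 43 / 0.9 = 47.8, rounded up to 48, for a total of 96.

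The stated total therefore fits a two-sided difference trial with 80% power and an SD near 10.5. This shows consistency, not proof, because the SD is back-solved.

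**How often the planned test is nonsignificant when one tracer is truly worse.** With 43 per arm, SE = SD × √(2/43), and for a true deficit of δ nodes

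P(nonsignificant) = Φ(1.960 − δ/SE) − Φ(−1.960 − δ/SE).

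| Assumed SD | SE | δ = 3 nodes | δ = 5 nodes |
|---|---|---|---|
| 8 | 1.73 | 0.59 | 0.17 |
| 10.5 | 2.26 | 0.74 | 0.40 |
| 15 | 3.23 | 0.85 | 0.66 |

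Example at SD 10.5 and δ = 3: 3 / 2.264 = 1.325, Φ(0.635) ≈ 0.737, and the second term is below 0.001, giving 0.74.

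The SD range of 8 to 15 is an assumption. The figure at δ = 6.41 is left out: at the back-solved SD it is about 20% by construction, which only restates the assumed type II error.

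**The case against.** Several arguments can be made for the plan, and some of them stand.

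- **A condensed article may omit a margin, a reference arm and a confidence-interval rule.** This stands. Their absence alone is not the point. The point is that the article does state its design, its sizing basis and its test, and these disagree. An unseen analysis plan cannot turn a test of equality at P<0.05 into a noninferiority test.
- **Two unequal means and a two-sided 0.05 level do not strictly rule out noninferiority.** This stands in part. Noninferiority sizing can assume a nonzero true difference, and a two-sided 95% interval matches a one-sided 0.025 test. A total of 96 would also fit a 6.41-node margin with equal true means at an SD of about 10.6. But section 2.7 presents 6.41 as the gap between expected group means, not as a margin.
- **Not everything in the article points to superiority.** This stands. The aim at the end of the Introduction is a neutral comparison of safety and efficacy.

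A reader might also infer three stronger things that the article does not support.

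- That the investigators intend to report a nonsignificant P as noninferiority. No section says so. The wording leaves that possible and no more.
- That the primary comparison has no decision rule. It has one, a P value below 0.05, but that rule belongs to a difference trial.
- That the trial is badly underpowered for noninferiority. That depends on the reference arm. At SD 10.5 and a 3-node margin, power is Φ(3/2.264 − 1.96) ≈ 0.26 if the true means are equal. It is Φ((3 + 6.41)/2.264 − 1.96) ≈ 0.99 under the planned means if CNSI is the tested arm. If ICG is the tested arm, no margin of 6.41 nodes or less can be powered under those means.

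**Conclusion.** The concern holds as an internal contradiction. The label in section 2.1 conflicts with the sizing in 2.7, the test in 2.8 and the goal in the Discussion, and nothing in the article reconciles them. The contradiction is in the text and needs no assumption about the SD.

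The size of the risk does depend on the SD. A nonsignificant result is likely with a true deficit of 3 nodes at every SD tried. With a deficit of 5 nodes it ranges from fairly uncommon at SD 8 to more likely than not at SD 15. These figures assume 43 evaluable patients per arm, the normal approximation to the t test, and an SD between 8 and 15.

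**What to change.** - In section 2.1, replace noninferiority with two-sided superiority (difference).
- In section 2.8, report the mean difference in nodes retrieved (CNSI minus ICG) with its 95% CI. State that a nonsignificant result is inconclusive and will not be called noninferior or equivalent.
- Because enrolment began in January 2021 and the Abstract reports 96 patients enrolled, record the change as a dated amendment that says whether outcome data had been seen.
- The noninferiority label can stay only if the full protocol already contains a reference arm, a margin and a confidence-interval rule, all fixed before any outcome data were seen. In that case, state them in the article and bring sections 2.7 and 2.8 into line with them.

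Relabelling needs no extra patients and leaves the planned test and the total of 96 unchanged. The costs are the amendment and the loss of any noninferiority claim.

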**Figure 1 f1:**
[figure not shown]
Flow chart.

### Eligibility criteria

2.2

The inclusion criteria are as follows: (1) aged 18–75; (2) histologically proven gastric adenocarcinoma on biopsy (papillary adenocarcinoma, tubular adenocarcinoma, mucous adenocarcinoma, signet-ring cell carcinoma or poorly differentiated adenocarcinoma); (3) proven clinical stage of cT1-4a N0/+ M0 by ultrasound endoscopy, enhanced CT/MRI examination or diagnostic laparoscopy according to the TNM classification of the American Joint Committee on Cancer (AJCC cancer staging manual, eighth edition); (4) without distant metastasis and no invasion of adjacent organs; (5) a preoperative Eastern Cooperative Oncology Group (ECOG) score of 0 or 1; (6) a preoperative American Society of Anesthesiologists (ASA) score of I-III; and (7) signed a written informed consent form.

The exclusion criteria are as follows: (1) pregnant or lactating women; (2) patients with severe mental disorder; (3) a history of upper abdominal surgery (with exception of laparoscopic cholecystectomy); (4) a history of gastrectomies, endoscopic mucosal resection (EMR) or endoscopic submucosal dissection (ESD); (5) enlarged or bulky regional LNs according to preoperative imaging and larger than 3 cm at the long diameter; (6) the tumor invades the duodenum or esophagus; (7) Borrmann type IV GC; (8) history of other malignant tumors within the last 5 years; (9) received previous neoadjuvant radiotherapy or chemotherapy; (10) history of myocardial infarction or unstable angina within the last 6 months; (11) history of cerebrovascular accident within the last 6 months; (12) undergoing sustained systemic corticosteroid treatment within 1 month prior to surgery; (13) emergency surgery due to GC complications (bleeding, perforation, or obstruction); and (14) FEV1 <50% predicted value.

### Randomization and blinding

2.3

The patients were enrolled by a dedicated surgeon on our team. For eligible patients treated with GC at The Fourth Hospital of Hebei Medical University, thoracoabdominal CT, echocardiography, ultrasound of supraclavicular LNs, sonography of lower extremity veins, electrocardiogram and lung function examination should be performed before the operation. The patients who meet the inclusion criteria and are feasible for radical onco-surgery are then randomized to receive either endoscopic injection of CNSI (CNSI group) or endoscopic injection of ICG (ICG group) during gastroscopy at a 1:1 ratio. Randomization has been achieved using a random number table by the data manager, and the allocation is not concealed. While the blinding of the surgeons or participants is impossible, the pathologists are blinded to the types of surgical approaches.

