### Outcomes

2.5

The primary outcome of this study is to determine the number of LNs retrieved. The secondary outcomes are to determine the LN staining (or fluorescence) rate (Number of staining or fluorescence LNs/Total number of retrieved LNs), LN staining (or fluorescence) rate at each station, stained (or fluorescent) LN positive rate(Number of staining or fluorescence positive LNs/Total number of positive LNs), stained (or fluorescent) LN negative rate(Number of staining or fluorescence negative LNs/Total number of negative LNs), nonstained (or nonfluorescent) LN positive rate(Number of nonstaining or nonfluorescence positive LNs/Total number of positive LNs), nonstained (or nonfluorescent) LN negative rate(Number of nonstaining or nonfluorescence negative LNs/Total number of negative LNs), LN metastasis rate(Number of metastasis LNs/Total number of retrieved LNs), number of metastatic LNs, complication and mortality rates within 30 days, 3-year disease-free survival (DFS), 3-year overall survival (OS), recurrence pattern within 3 years, intraoperative blood loss volume, time spent retrieving LNs, and postoperative recovery (exhaust time after surgery, feeding time after surgery, duration of postoperative hospital stay).

Any complications should be recorded and reported. There are mainly two complications related to the procedure: intraoperative complications and postoperative complications. The former includes bleeding, injuring the viscera, lymphatic leakage and so on. The latter should be classified according to the Clavien−Dindo classification system.

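### The protocol states that allocation is not concealed while a surgeon of the trial team enrols, so, read literally, the randomized comparison lacks protection against selection at enrolment

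*Protocol article*

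**What the plan says.** The protocol article covers entry and assignment in one paragraph (section 2.3, Randomization and blinding):

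- On enrolment: "The patients were enrolled by a dedicated surgeon on our team".
- On the step before assignment: "The patients who meet the inclusion criteria and are feasible for radical onco-surgery are then randomized to receive either endoscopic injection of CNSI" or the ICG injection, at 1:1. The article does not say who judges feasibility.
- On the sequence: "Randomization has been achieved using a random number table by the data manager, and the allocation is not concealed".
- On blinding, in the sentence after that: "While the blinding of the surgeons or participants is impossible, the pathologists are blinded to the types of surgical approaches".

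Section 2.1 has already given the design: "The current study is a prospective, randomized, open label, single-center, noninferiority clinical trial". The primary outcome is the number of lymph nodes retrieved (section 2.5). For continuous data, section 2.8 plans a baseline comparability analysis and an independent-samples t test or a nonparametric test. It mentions examining other factors that influence node count, but specifies no adjusted primary comparison.

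**The concern.** Blinding and allocation concealment are separate safeguards. Blinding acts after assignment and cannot be achieved here for surgeons or patients. Concealment acts before assignment: whoever decides on entry must not be able to foresee the arm. It is available in any open-label trial, so the open-label design does not explain its absence.

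If the next arm could be foreseen, a patient expected to give a high or low node yield could be entered, deferred or passed over accordingly. The arms would then differ at baseline for reasons other than chance. Nothing later in the plan removes such a difference. Pathologist blinding acts too late, a baseline comparability check in 96 patients is insensitive to modest imbalance and blind to unrecorded factors, and the planned test is unadjusted.

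The Introduction also reports a preference from the team's retrospective work: "Hence, we concluded that CNSI was more likely to be the best LN tracer at present". That makes the safeguard more valuable, although it does not show that anyone acted on the preference.

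**Working it through.** **Step 1: is the sentence just another way of saying open label?** Section 2.1 already gives the open-label design, and section 2.3 handles blinding in its own sentence directly after the one on concealment. On a plain reading, the concealment sentence therefore adds something: the sequence was not hidden. It is a positive statement, not a detail that a condensed article has left out.

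**Step 2: what the text establishes and what it leaves open.**

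| Point | Status in the article |
|---|---|
| Concealment absent | Stated |
| Enrolment by a surgeon of the team | Stated |
| Sequence handled by the data manager | Stated |
| Randomization follows the eligibility and feasibility step | Stated |
| Any safeguard at release of the arm | None described |
| Enrolling surgeon saw the list or knew the next arm | Not stated |
| Enrolling surgeon made the feasibility judgement | Not stated |
| Baseline imbalance occurred | Not stated |

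**Step 3: background to the sample size.** Section 2.7 gives means of 56.93 and 50.52, 48 per group after 10% dropout, and "All analyses were two-sided with α=0.05 and β=0.80", where I read 0.80 as the power. It gives no SD, so 96 cannot be reproduced independently. The SD can be back-solved:

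- Difference: 56.93 − 50.52 = 6.41.
- Evaluable per arm: 43, since 43 / 0.9 = 47.8, rounded up to 48.
- SD = 6.41 / [(1.960 + 0.842) × √(2/43)] = 10.6. An SD of 10.5 also rounds up to 43 per arm.

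This SD is an inference. I also use 15 and 20, which are assumptions, to show how the result depends on it.

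**Step 4: illustration of what is at stake.** Suppose that there is no true difference and that selection shifts the mean difference by b nodes. The article gives no value for b. As one assumed route to such values, a factor worth 10 nodes that differs by 20 percentage points between arms gives b = 10 × 0.20 = 2.0, which is 31% of 6.41. A 30-point difference gives b = 3.0.

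The two-sided rejection rate of the z test is

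P = 1 − [Φ(1.96 − b/SE) − Φ(−1.96 − b/SE)], with SE = SD × √(2/43).

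At SD 10.6, SE = 2.286. For b = 2, b/SE = 0.875 and P = 0.141.

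| SD | b = 0 | b = 1 | b = 2 | b = 3 |
|---|---|---|---|---|
| 10.6 (back-solved) | 0.050 | 0.072 | 0.141 | 0.259 |
| 15 (assumed) | 0.050 | 0.061 | 0.095 | 0.153 |
| 20 (assumed) | 0.050 | 0.056 | 0.075 | 0.107 |

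At SD 10.5 (SE = 2.264) the last two entries of the top row become 0.143 and 0.263. The illustration uses a two-sided test of difference because that is what section 2.8 plans; the article states no noninferiority margin.

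**The case against.** The strongest reply is that the sentence is loosely worded. It sits beside the statement on blinding and may mean only that the assigned arm was known once given. The data manager, not the enrolling surgeon, ran the random number table, and randomization came after eligibility. The Introduction follows the remark favouring CNSI with the limits of retrospective data as the reason to randomize, and the Discussion lists advantages of ICG as well. The imbalance in the illustration has no source in the article.

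Much of this stands. A reader might infer that the enrolling surgeon knew the next arm and steered patients towards CNSI. The article does not support that: it says neither who could see the list nor who judged feasibility, and it attributes the preference to the team. A reader might also take 14% or 26% as the trial's actual error rate; these are the upper end of an assumed range.

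The reply does not remove the point. If only knowledge of the arm after assignment was meant, the sentence says something else and needs correcting. If it was meant literally, a basic safeguard was missing. A separate data manager helps only if the arm was withheld until entry was settled, and the article does not say that it was.

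**Conclusion.** The point holds as a stated lack of a safeguard, or else as a wrong sentence about one that existed. Either way the protocol has to resolve it. It does not hold as a finding of selection bias.

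The possible size depends on two unknowns, the SD and any induced imbalance. Over SDs from 10.6 to 20, an assumed 2-node shift gives a false-positive rate of about 7.5% to 14%, and a 3-node shift about 11% to 26%, against a nominal 5%. Without any imbalance the rate stays at 5%.

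Timing limits what can be done. The Abstract says that 96 patients, the full target, have been enrolled, so a concealment procedure introduced now would probably protect few or none. What remains is clarification, an analysis less exposed to baseline differences, and a conclusion that reflects the weakness.

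**What to change.** 1. In section 2.3, state who held the sequence, who could see it, and at what point the arm was released. If it was withheld until consent and eligibility were settled, correct the sentence; nothing more is then needed.
2. If concealment was absent, make the primary comparison of node count one that is adjusted for baseline factors fixed before assignment, named in advance. Examples are age, sex, clinical stage and tumour location, where these were recorded before assignment. Section 2.8 takes tumour location from pathology and operative reports, so a preoperative record should be used if there is one. A factor recorded after the arm was known cannot be relied on to remove the bias.
3. Keep the unadjusted test as a sensitivity analysis.
4. If a screening log exists, report the patients who were eligible but not randomized.
5. State the lack of concealment as a limitation on the conclusion. Adjustment deals only with measured factors.
6. For any patient still to be randomized, the data manager releases the arm only after consent and eligibility are recorded.

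The cost is a few sentences in the protocol, a little more analysis work, retrieval of preoperative records where they exist, and a more cautious conclusion. No new staff are needed.
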